# Trial synopsis

Title: RESTRICTIVE VERSUS LIBERAL OXYGENATION TARGETS IN PATIENTS WITH ACUTE HEART FAILURE AND PULMONARY CONGESTION – A RANDOMIZED CLINICAL PILOT-TRIAL

Background:

One million hospitalizations occur each year with a primary diagnosis of acute heart failure in the USA, with comparable numbers in Europe. Most patients with acute heart failure are treated with supplemental oxygen during hospitalization and guidelines recommend initiation of oxygen therapy if SpO2 <90% (class I, level C). However, no clinical trials of oxygen targets in humans with acute heart failure investigating clinically relevant endpoints have been performed.

Primary objective:

To investigate the effect of a restrictive vs. liberal oxygenation-strategy in patients hospitalized with acute heart failure.

Hypothesis:

Restrictive oxygenation is associated with improved clinical outcome compared to liberal oxygenation.

Design: Investigator-initiated, prospective, randomized, blinded, multi-center, controlled trial.

Intervention:

Patients will be randomized 1:1 in the emergency department to either liberal or restrictive oxygenation after providing informed written consent.

(1) Liberal oxygenation group = SpO2 target of 96%.

(2) Restrictive oxygenation group = SpO2 target of 90%.

Patients will have nasal cannula or oxygen mask placed as the usual care, and oxygen is titrated to the prespecified target range.

Consented patients will be randomly allocated to study groups via the automated web-based system within REDCap. The allocation will be concealed. Time at randomization will be considered as study time zero (T0). All patients will receive usual standard of care except for their oxygen-administration.

The intervention-phase will be 24 h, and hereafter oxygen therapy will be at the discretion of the treating physician.

Inclusion criteria:

1. Age ≥ 18 years
2. Acute (within minutes to days) onset or worsening of subjective dyspnea
3. Oxygen saturation <92% (on arterial blood gas) or need of oxygen
4. At least one of the following clinical or radiological signs of congestion:
   - - 1. Pulmonary rales
       2. Chest X-ray or CT with pulmonary congestion
       3. Lung ultrasound with multiple B-lines

Exclusion criteria:

1. More than 4 hours from hospital admission to randomization
2. Suspected infection or sepsis
3. Known severe pulmonary disease
4. Systolic blood pressure <90 mmHg

Primary outcome:

Pulmonary parenchymal fluid content after 24 hours preceded by 10 minutes without oxygen-supplementation.

Secondary outcomes:

1. Arterial blood gas concentration after 24 hours preceded by 10 minutes without oxygen-supplementation.
2. All-cause mortality at day 30
3. Days alive out-of-hospital to day 30
4. Time to freedom from oxygen-supplementation

Sample Size/Study Duration:

To have 90 % power to find a difference of 4 % in lung fluid content (change from 39.8% to 35.8%) at 24 hours with a standard deviation of 6.8, we need to include **122 patients (61 in each group).** The α-level is 0.05, and the beta is 10%. We expect minimal dropouts. The study will include patients over an estimated period of 1 years in two centers.

#

## 1.4 Official Approvals

Datatilsynet, En-Suite nummer: P-2022-770Ethical committee number: H-22062699

ClinicalTrials.gov number: NCT05613218

## 1.5 Data Safety Monitoring Board

No DSMB will be needed for this trial.

# 2. Background

Acute heart failure is a leading cause of hospitalizations in patients aged >65 years and over one million emergency department hospitalizations occur each year with a primary diagnosis of acute heart failure in the USA, with comparable numbers in Europe [3, 4]. In USA, heart failure is the most expensive reason for admission and re-admission for older patients [5]. With increasing age this burden will likely continue to rise [6]. Up to a third of patients hospitalized with acute heart failure will die or be re-hospitalized within 3 months [7–10]. The continued poor outcome for acute heart failure is in contrast to the progress made in other cardiovascular fields, such as chronic heart failure and acute coronary syndrome [11].

Heart failure is a chronic syndrome characterized by symptoms and clinical findings such as dyspnea, pulmonary and systemic congestion [12]. The syndrome is a consequence of myocardial dysfunction or structural cardiac disease that may lead to either of or a mixture of forward and backward failures [12]. An acute heart failure-episode is seen when heart failure present itself de novo with abrupt symptoms leading to an emergency department visit or when patients with known heart failure have an acute exacerbation requiring hospitalizing [13]. Acute heart failure refers to rapid onset of symptoms and clinical signs of heart failure leading to an unplanned hospital admission or an emergency department visit [12]. Patients with acute heart failure should be evaluated immediately and subsequent treatment administered in the acute setting within the first few minutes to hours [12].

Four main clinical presentations are emphasized in 2021 European guidelines for heart failure. The four phenotypes can be separated based on the presence of signs of congestion (no congestion = dry; congestion = wet) and/or peripheral hypoperfusion (normoperfusion = warm; hypoperfusion = cold) and may require different treatments [12]. Acutely decompensated heart failure is the most common form of acute heart failure, accounting for 50-70% of presentations [14]. Acute pulmonary oedema occurs in 13-25 % of presentations [15]. <5 % presents with isolated right ventricular failure or cardiogenic shock [14, 15]. The division into phenotypes is mostly academic and guidelines emphasize that overlaps between them should be considered. Besides isolated RV-failure, pulmonary congestion with or without systemic congestion is a main characteristic of acute heart failure and is present in above 50% of cases.

Treatment of pulmonary congestion

Despite the critical importance of initial management, data are sparse regarding the impact of early treatment delivered in the emergency department [13]. Current guidelines recommend three therapies to be commenced: First, oxygen and/or continuous positive airway pressure / non-invasive positive-pressure-ventilation. Second, i.v. diuretics, and third, i.v. vasodilators may be considered when SBP is >110 mmHg (previous guidelines had 90 mmHg as cutoff [16]), to reduce LV afterload.

Lung fluid content

The ability to quantify the degree of pulmonary congestion in AHF can help guide treatment and the pulmonary water content can be assessed noninvasively by the remote dielectric sensing (ReDS) device (Sensible Medical, Netanya, Israel). ReDS is an FDA-approved, wearable device developed by Sensible Medical Innovations that allows clinicians and other health care providers to quickly and accurately measure lung fluid in patients, noninvasively. The lung fluid content is measured within the mid-region of the right lung. The measurement is presented as the percentage of the lung volume composed of fluid, (normal values for non-congested people is 20%-35% of fluid content) [25]. This novel noninvasive electromagnetic energy-based technology [26] is intended to quantify changes in lung fluid content. The device measures the dielectric properties of tissues. Low power electromagnetic signals are emitted across the thorax through the lung and the characteristics of the signals received after passing through the tissue are related to their dielectric properties which, in turn, are mostly determined by the lung's fluid content. The dive is superior to bio-impedance-based devices which are affected by many factors in addition to lung fluid content (e.g., electrode placement, body habitus, fat content, skin moisture) and doesn’t have the need for electromagnetic radiation associated with chest CT. In a validation study of acute heart failure patients, fluid content quantified by ReDS™ was highly correlated to chest CT [26].

Oxygenation

Supplemental oxygen therapy has been used for more than a century and is a routine treatment in the management of patients with dyspnea in the emergency department, including those with acute heart failure (AHF) [17]. Even in absence of the arterial hypoxemia, oxygen is often administered in these patients on the basis of the clinicians’ or patients’ belief that it will improve organ oxygenation [17]. Current guidelines recommend the initiation of oxygen therapy (class 1,c) as part of initial treatment [12] if SpO2 <90% or PaO2 <60 mmHg to correct hypoxemia. However, there is a remarkable absence of clinical evidence in this area of treatment [12]. While there is consensus among guideline-writers regarding the treatment of severe hypoxaemia (low O2 saturation levels or SpO2), it is unclear whether oxygen should be administered in absence of severe hypoxemia.

Oxygen is a pulmonary vasodilator, and higher oxygen concentrations is associated with lower pulmonary vascular resistance. This may theoretically unload a failing right ventricle, which can be an advantage in cases of increased RV-afterload, such as acute pulmonary embolism. Contrary, it is believed that hyperoxemia should be avoided, as it causes systemic vasoconstriction including brain and myocardium, and a reduction in cardiac output in high doses [18]. Several physiologic studies have suggested deleterious effects of hyperoxia on cardiac function [19]. In general oxygen is considered a systemic arterial vasoconstrictor and associated with reduced coronary blood flow and myocardial oxygen consumption [19, 20]. In 10 patients with congestive heart failure Haque et al. showed a reduction in cardiac output, stroke volume and increase in pulmonary capillary wedge pressure and systemic vascular resistance when administrated 100% oxygen on a face mask [20]. Mak et al. gave 100% oxygen to two groups of patients with and without heart failure and found hyperoxia associated with increased LV filling pressures in both patient-groups irrespective of heart failure. The authors concluded, that caution should be used in the administration of inspired oxygen to normoxic patients, especially in the setting of heart failure [21]. ESC 2021 guidelines for heart failure recommend oxygen therapy to be initiated first of all treatments in hypoxemic AHF. Yet guidelines are cautious regarding recommendations on the use of supplemental O2 therapy in non-hypoxaemic patients with AHF. The guidelines cite just one study by Park et al. of 13 patients with chronic heart failure, where oxygen administration was shown to cause vasoconstriction and a reduction in cardiac output [18]. Of note, no clinical studies of oxygen in acute heart failure are cited by contemporary guidelines and yet oxygen is recommended if SpO2 <90% or PaO2 <60 mmHg [12]. In a recent large trial of resuscitated cardiac arrest patients, a low oxygenation target did not result in different outcome compared with a higher oxygenation target [22]. In a large trial of oxygen therapy in suspected acute myocardial infarction, Hofmann et al. found no benefit of routine use of supplemental oxygen [23].

In a pilot-trial by Sepehrvand et al., 25 patients with AHF were allocated to high (≥96%) and 25 patients to low (90–92%) SpO2 targets [24]. They found no differences in key primary or secondary endpoints, which the trial was underpowered for, but saw a significant prolonged hospital length-of-stay in the low target group (p=0.01) [24]. One limitation to that trial, beside the small sample size, was the time from admission to inclusion in the trial of median 11.4 (IQR 7.3, 13.5) hours.

Several therapeutic goals for patients admitted with pulmonary congestion are pertinent. Since patients suffer from severe dyspnea, a rapid relieve should be one therapeutic goal. Additionally, since a more targeted emergency treatment will potentially reduce the need for mechanical ventilation and intensive care admissions, another goal is to decrease hospital length of stay. Still, such achievements should transpire without patients experiencing organ hypoxemia or worsening heart failure in the days after the initial treatment. Adverse reactions to the treatment, such as hypoxemia or hypercapnia, should be balanced with the potential benefit in the emergency setting. Previous studies of acute heart failure have included patients up to and above 11 hours post-admission, why trial-based evidence to guide treatment in the first hours of admission is non-existing.

The effects of oxygen administration for acute heart failure in the emergency setting are still unknown and a clinical equipoise exist between restrictive or liberal oxygenation. The different strategies should be investigated in prospective trials to optimize acute treatment.

# 3. Trial objectives and hypotheses

To investigate the effect of a restrictive vs. liberal oxygenation-strategy on outcomes in patients hospitalized with AHF.

Hypothesis:

Restrictive oxygenation is associated with improved outcome compared to liberal oxygenation.

# 4. Study design

The study is an investigator-initiated, prospective, randomized, blinded, multi-center, controlled trial. Following successful completion of screening procedures, patients will be randomized in a 1:1 fashion to receive either of the 2 treatments-strategies.

# 5. Intervention

Random allocation to 1 of 2 strategies:

- Liberal oxygenation group = SpO2 target of 96%.
- Restrictive oxygenation group = SpO2 target of 90%.

5.1 Detailed intervention and suggested initial treatment

Immediately after admission, the standard of care-treatment can be initiated as per discretion of the treating physician. Oxygen can be administered freely. The attending physician at the site will assess the patient’s eligibility for inclusion in the trial. After successful screening, the patient will be asked for written informed consent from study investigators. The sites will aim to obtain the consents as soon as possible. Patients will have nasal cannula or oxygen mask placed as the usual standard of care.

Patients will be screened and randomized in the emergency department to either liberal or restrictive oxygenation after providing informed written consent and oxygen is titrated to the prespecified target range using an automated feedback device (O2MATIC). Consented patients will be randomly allocated to study groups via the web-based system within REDCap. The allocation will be concealed. Time at randomization will be considered as study time zero (T0). All patients will receive usual standard of care except for their O2 management. The intervention will last for 24 h. After 24 h, patients will be switched over to usual care for oxygen therapy. We selected the 24 h time frame because in previous studies most patients with AHF were no longer on oxygen after 24 h [27]. If the treating physician thinks, that the patient need another oxygenation target and it is thought to be harmful to continue with the allocated target, the intervention-phase can be stopped prematurely.

Blinding

The intervention will be administrated double-blinded using the O2MATIC-device, which will titrate the oxygen-supplementation towards the intended target SpO2 without it being visible for patients, investigators or treating personnel. The robot will be programmed to deliver the intervention, record minute-by-minute data of oxygen-supplementation and SpO2. Furthermore, the robot will give an alarm if SpO2 drops below 88%. During the intervention-phase, SpO2 will not be measured by the nurses.

#### Titration of oxygen using an automated feed-back device (O2matic) for patients with acute heart

#### failure needing oxygen-therapy

A Danish research group has developed a closed-loop system for oxygen-administration, O2matic, which is developed at Hvidovre Hospital, Denmark [28]. The first prototypes have been tested at the Copenhagen Academy of Medical Education and Simulation (CAMES), where it has been found in simulation models of COPD exacerbations that O2matic is better than fixed oxygen dosage to keep the oxygen saturation within the desired range. O2matic developed and manufactured in a version that is in accordance with the requirements of the Medical Device Directive product has been CE marked. It has also been tested in a recorded and controlled clinical study in which automated and continuous oxygen monitoring was assessed versus manual control in patients with inpatient exacerbation of COPD.

# 6. Setting and patient population

## 6.1 Setting

The trial includes patients in the acute emergency setting. All patients are included in-hospital in the associated emergency departments. Patients are recruited from participating centers by the attending cardiologist or emergency physician. The first patient-contact is passed on from clinical staff to the research group, as the research group prior to obtaining consent do not have access to patient records. The first contact is made via the clinical staff, so that a potential trial participant has the option to decline further information about the project before contact are made from the research group. From trial initiation, all patients admitted to the sites’ EDs will be entered in a screening log, either by part of the inclusion and randomization process or post hoc. The screening log will include patient’s ID, demographic data, and reasons for not including the patients in the trial (lack of inclusion criteria, presence of exclusion criteria, logistical reasons, in that order).

## 6.3 Inclusion criteria

1. Age ≥ 18 years
2. Acute (within minutes to days) onset or worsening of subjective dyspnea
3. Oxygen saturation <92% or need of oxygen
4. At least one of the following (clinical or radiological signs of congestion):
   1. Pulmonary rales
   2. Chest X-ray or CT with pulmonary congestion
   3. Lung ultrasound with multiple B-lines

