## 7.3 Eksploratory outcomes

1. Change from baseline in log-transformed biomarkers (N-Terminal Pro-Brain Natriuretic Peptide (NTproBNP), troponin T, creatinine, neuron-specific enolase, procalcitonin) to 24 hours from admission.
2. 2D and 3D systolic and diastolic strain parameters (i.e. time to peak strain, systolic and diastolic strain rates, displacements, velocities, torsion) and traditional TTE measures as well such as ventricular volumetry and function, stroke volume derived from the velocity time integral of the left ventricular outflow tract, tissue doppler and mitral valve inflow patterns to assess diastolic function, right ventricular fractional area change and tricuspid annular plane systolic excursion.
3. Days alive out-of-ICU until day 30
4. Patient-reported dyspnea on a VAS-scale 1-100 after 24 hours
5. Number of patients where intervention is terminated (opt out) before 6 hours
6. Time within targeted SpO2-interval (89-91 % in restrictive group, 95-97% in liberal group)
7. Multiple B-lines in at least two areas on lung ultrasound identifying interstitial syndrome (yes/no).
8. FiO2, Blood pressure, respiratory rate, heart rate after 24 hours
9. Quality of life and depression: HADS, SF-36 and EQ-5D-5L

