# 8. Sample size calculations and statistical analysis plan

In a validation-trial of ReDS, Amir et al investigated 16 patients with acute heart failure and found a mean fluid content of 39.8 + 6.8 % [25]. Similar results were seen when estimating fluid content by the chest CT, which is regarded as the gold standard.

To have 90 % power to find a difference of 4 % in lung fluid content (change from 39.8% to 35.8%) with a standard deviation of 6.8, we need to include 122 patients (61 in each group). The α-level is 0.05, and the beta is 10%. We expect minimal dropouts. The study will include patients over an estimated period of 1 years in two centers. We will include patients until we have reached the estimated sample size without any missing values in the primary outcome, to ensure that we can conclude on our primary hypothesis.

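### No inclusion criterion requires acute heart failure, so patients outside the stated objective could be randomised and would stay in the primary analysis

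*Protocol*

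**What the plan says.** The synopsis title names "PATIENTS WITH ACUTE HEART FAILURE AND PULMONARY CONGESTION". Section 3 gives the objective as "To investigate the effect of a restrictive vs. liberal oxygenation-strategy on outcomes in patients hospitalized with AHF". Section 8 takes its planning mean and SD for lung fluid content (39.8% and 6.8) from a ReDS validation study of 16 patients with acute heart failure.

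Section 6.3 sets four conditions, and the synopsis gives essentially the same list:

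- age 18 years or more;
- "Acute (within minutes to days) onset or worsening of subjective dyspnea";
- "Oxygen saturation <92% or need of oxygen";
- "At least one of the following (clinical or radiological signs of congestion": "Pulmonary rales", congestion on chest X-ray or CT, or multiple B-lines on lung ultrasound.

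Section 6.4 excludes late randomisation, suspected infection or sepsis, low systolic pressure and, on the pulmonary side, only severe COPD that is already known. The synopsis words the pulmonary exclusion more widely, as known severe lung disease in general.

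Section 12 (statistical analyses) defines the modified intention-to-treat set as randomised patients who meet the inclusion criteria, less those whose consent is withdrawn.

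**The concern.** The question the trial asks is about AHF. The group it admits has acute hypoxaemic dyspnoea with at least one sign taken as congestion. The two groups overlap heavily but are not the same. No criterion asks for a suspected or working diagnosis of AHF, a natriuretic peptide level or an echocardiographic finding. Rales can have non-cardiac causes. Section 7.3 ties B-lines to a wider label than AHF: "Multiple B-lines in at least two areas on lung ultrasound identifying interstitial syndrome (yes/no".

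Two things are at stake. If some enrolled patients do not have AHF and respond less, the average 24-hour ReDS difference shrinks below the 4 points planned for, and power falls. Whatever the size of that effect, the result describes a mixed group, while the report would describe patients with AHF.

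**Working it through.** **1. Does any part of the protocol make AHF a condition of entry or analysis?**

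| Place | What it contributes | AHF required? |
|---|---|---|
| Title, section 3 | Names AHF as the target | Intended, but not an entry rule |
| Section 6.3, synopsis | Age, dyspnoea, saturation or oxygen need, one sign | No |
| Section 6.4, synopsis | Removes some look-alikes (infection, severe COPD or severe lung disease) | No |
| Sections 5.1 and 6.1 | Attending physician assesses eligibility and recruits | No AHF condition stated |
| Screening form (data collection section) | Criteria met, yes/no; investigator finds patient eligible, yes/no | No AHF item |
| Appendix 2 | Check the criteria, consent, randomise | No |
| Section 12, analysis set | Follows the inclusion criteria | No |
| Section 12, covariates and subgroups | History of heart failure, NT-proBNP, LVEF | Describes patients, does not select them |

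Nothing after section 6.3 closes the gap.

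**2. Reproduce the planned sample size.** Inputs from section 8: difference 4, SD 6.8, alpha 0.05, power 90%. Two-sided testing is from section 12 and 1:1 allocation from section 4.

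n per arm = 2 × (1.960 + 1.282)² × 6.8² / 4² = 60.7, rounded up to 61, so 122 in total. This matches the protocol. With 61 per arm, power is 0.901 by the normal approximation and 0.897 by the two-sample t-test. The arithmetic is right; the question is whether inputs from AHF patients fit the group enrolled.

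**3. Illustrate the dilution.** Let f be the share of enrolled patients without AHF. The documents give no value for f. Assume the extreme case of no treatment effect in these patients, and keep the SD at 6.8.

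Expected difference = 4 × (1 − f). Standard error = 6.8 × √(2/61) = 1.231.

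| f | Difference | Difference / SE | Power, t-test, 61 per arm | Total N for 90% power (normal approximation) |
|---|---|---|---|---|
| 0% | 4.0 | 3.25 | 0.897 | 122 |
| 10% | 3.6 | 2.92 | 0.826 | 150 |
| 20% | 3.2 | 2.60 | 0.732 | 190 |
| 30% | 2.8 | 2.27 | 0.616 | 248 |

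**4. Relax the extreme assumption.** If non-AHF patients had half the effect, f = 20% would give 4 × (1 − 0.2 × 0.5) = 3.6. That is the 10% row, with power about 83% instead of 73%.

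**The case against.** The best defence is that entry is deliberately syndromic. Section 2 describes AHF as rapid onset of symptoms and signs of heart failure leading to unplanned hospital contact. Criterion 2 captures the rapid onset, and criterion 4 is labelled as signs of congestion, so a sign is meant to count only as congestion. Randomisation must happen within 4 hours of admission, which favours simple criteria. A cardiologist or emergency physician recruits, and the screening form has a separate field for the investigator's own view of eligibility, which leaves room for judgement beyond the checklist. All of this stands and makes the problem smaller in practice. It does not make AHF a condition of entry, and eligibility is fixed in the protocol, not left to a statistical analysis plan.

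A reader might infer more than the documents support:

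- *That sites would enrol many non-AHF patients.* The text shows only that they could. Under the synopsis wording, known severe interstitial lung disease is excluded; under section 6.4 it is not.
- *That oxygen cannot act outside AHF.* Section 2 cites a study in which high oxygen raised left ventricular filling pressure with or without heart failure. Zero effect is therefore a bound, not an expectation.
- *That non-AHF patients would have normal ReDS values and so inflate the SD.* Sections 2 and 9 give the 20–35% range for people without congestion, whom criterion 4 is meant to keep out.
- *That the recruitment forecast rests on the wrong group.* Section 8.1 applied the current criteria to a dyspnoea cohort, so the forecast is consistent with them.
- *That the planning figures come from patients with a verified diagnosis.* Section 8 says only that they had acute heart failure, not how it was established.

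**Conclusion.** The point holds as a mismatch between objective and eligibility. Following the protocol as written can put patients without AHF into the trial and its primary analysis. The comparison between arms stays valid; the possible harm is to power and to how far the result applies to AHF. The size cannot be fixed from the documents, because the share of such patients and their response are both unknown. Under the extreme assumption of no response and an unchanged SD, power would be about 83%, 73% or 62% at shares of 10%, 20% or 30%; any response in these patients makes the loss smaller. The change is worth making because it is cheap and brings the enrolled group into line with the objective, not because a large loss has been shown.

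Separately, the pulmonary exclusion differs between the synopsis and section 6.4. This decides which patients with lung disease can enter, so the two must be reconciled.

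**What to change.** **Main change.** Add one line to section 6.3, the synopsis, the pocket card and the REDCap screening form: acute heart failure is, in the attending physician's judgement, the most likely cause of the dyspnoea. Make the pulmonary exclusion read the same in the synopsis and section 6.4.

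**Optional.** Prespecify a supportive analysis of the primary outcome in patients whose AHF is supported by pre-randomisation NT-proBNP and echocardiography, classified blind to allocation, with all randomised patients kept in the main analysis. Appendix 4 schedules routine bloods and echocardiography at baseline, and NT-proBNP is in the routine panel. The emergency-department data list, however, records echocardiography only where available, so the rule must say how patients without it are classified. Appendix 2 places study procedures after the randomisation step, so the rule should also state which measurements count as baseline.

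**Cost.** One line of text in four places, and at most one extra analysis on data already planned. Some dyspnoeic patients without a working diagnosis of AHF would no longer be enrolled, so recruitment may be slightly slower.
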